## Abstract

**Background:**

Advance care planning (ACP), a process of communication about patients’ preferences for future medical care, should be initiated in a timely manner. Ideally situated for this initiation is the general practitioner (GP). The intervention to improve the initiation of ACP for patients with a chronic life-limiting illness in general practice (ACP-GP) includes an ACP workbook for patients, ACP communication training for GPs, planned ACP conversations, and documentation of ACP conversation outcomes in a structured template. We present the study protocol of a Phase-III randomized controlled trial (RCT) of ACP-GP that aims to evaluate its effects on outcomes at the GP, patient, and surrogate decision maker (SDM) levels; and to assess the implementation process of the intervention.

**Methods:**

This RCT will take place in Flanders, Belgium. Thirty-six GPs, 108 patients with a chronic, life-limiting illness, and their (potential) SDM will be recruited, then cluster-randomized to the ACP-GP intervention or the control condition. The primary outcome for GPs is ACP self-efficacy; primary outcome for patients is level of ACP engagement. Secondary outcomes for GPs are ACP practices, knowledge and attitudes; and documentation of ACP discussion outcomes. Secondary outcomes for patients are quality of life; anxiety; depression; appointment of an SDM; completion of new ACP documents; thinking about ACP; and communication with the GP. The secondary outcome for the SDM is level of engagement with ACP. A process evaluation will assess the recruitment and implementation of the intervention using the RE-AIM framework.

**Discussion:**

While the general practice setting holds promise for timely initiation of ACP, there is a lack of randomized trial studies evaluating the effectiveness of ACP interventions implemented in this setting. After this Phase-III RCT, we will be able to present valuable evidence of the effects of this ACP-GP intervention, with the potential for offering a well-tested and evaluated program to be implemented in general practice. The results of the process evaluation will provide insight into what contributes to or detracts from implementation success, as well as how the intervention can be adapted to specific contexts or needs.

**Trial registration:**

Prospectively registered at with ISRCTN (ISRCTN12995230); registered 19/06/2020.

**Supplementary Information:**

The online version contains supplementary material available at 10.1186/s12904-021-00796-1.

## Background

Advance Care Planning (ACP) refers to “a process that supports adults at any age or stage of health in understanding and sharing their personal values, life goals, and preferences regarding future medical care” [1]. This may include the completion of a living will or Advance Directive (AD), which document wishes for future care should patients be unable to make their wishes known due to declining health or incapacity; and/or the appointing of a surrogate decision-maker (SDM), who can make care decisions in the place of the patient if the patient is unable to speak for themselves. ACP can lead to greater concordance between care preferences and care received [2], improved communication about the end of life with care providers [3], greater satisfaction with physician visits [4], and improved quality of end-of-life care [5]. It is a prerequisite for a good coordination of care, including palliative and end-of-life care, by making clear which medical decisions will be considered appropriate when the patient is unable to make such a decision themselves [6].

For patients with chronic, life-limiting illness (es), which are often marked by trajectories of steady illness progression or gradual health decline punctuated by acute deterioration [7], it is important that ACP is initiated in a timely manner so that sufficient time can be dedicated to conversations about values, goals and preferences [8]. ACP is intended as a continuous process of communication. For patients, engaging in ACP is not an isolated occurrence [9], but a complex behavior where readiness to engage in discrete behavior is an important precursor to action [10]. Especially suited to initiating these interactive discussions over multiple visits is the general practice setting. In Belgium, as in many other European countries, general practitioners (GPs) observe the patient’s health over the course of regular visits, often have a trusting relationship with the patient, and often are aware of the patient’s medical and social context [11, 12]. However, while the role of the GP in initiating ACP conversations is highlighted in guidelines of care [13], currently the process of ACP between patients and GP is not often initiated [14].

There is a lack of adequate practice models of initiation and implementation of ACP in general practice, and randomized trial studies evaluating the effectiveness of ACP interventions implemented in this setting are still largely absent. In light of this, a complex intervention for general practice has been developed [15, 16], and had subsequently been pilot-tested. The intervention was found to be feasible and acceptable. Based on the results of the pilot test, the intervention was adapted and is now being tested in a Phase-III trial [17]. This manuscript presents the research protocol for the Phase-III randomized controlled trial (RCT) study of the intervention. The Standard Protocol Items: Recommendations for Interventional Trials (SPIRIT) statement was applied to describe all relevant aspects of the trial (see Additional file 1) [18, 19].

### Objectives

The aim of this study is: To evaluate the effectiveness and mechanisms of action of a complex, multi-component ACP intervention, called ACP-GP, for patients with chronic, life-limiting illness (es), in the general practice setting, aimed at improving the readiness of patients to engage with ACP. The intervention will be compared to care as usual. Study objectives are:

**Table Taba:** 

(1) To **test** the effectiveness of the ACP-GP intervention on: • the patient’s level of engagement with ACP (primary outcome at patient level) • the GP’s self-efficacy for conducting ACP (primary outcome at GP level) (2) To **explore** the effect of the ACP-GP intervention on: • patient quality of life; symptoms of anxiety; symptoms of depression; the appointment of a substitute decision-maker; completion of new ACP documents; thinking about ACP, and communication with the GP (secondary outcomes at patient level) • GP ACP practices, attitudes and knowledge about ACP, and the documentation of ACP discussions in the patient medical file (secondary outcomes at GP level) • the SDM’s level of engagement with ACP (secondary outcome at the SDM level) (3) To **evaluate** the recruitment and implementation process of the intervention in terms of its reach, efficacy, adoption, implementation, and maintenance; as reported by patients, their SDM if present, and GPs	

### Trial design

This study is a 2-arm cluster-RCT with a parallel group design, which compares the ACP-GP intervention (arm 1) to usual care (arm 2) of patients with a chronic life-limiting illness. It is a superiority trial which aims to establish whether the intervention is superior to usual care in its effectiveness. GPs, their patients, and the (potential) SDM of each patient will be recruited for participation. Randomization occurs at the level of the GP, with patients and their SDM clustered per GP. To determine effectiveness, outcomes will be measured at baseline (T0), during a first follow-up at 3 months (T1) and again at 6 months post-baseline (T2).

A process evaluation will be used to evaluate how the intervention was implemented and to understand which factors contributed to the results of the trial. This process evaluation follows the RE-AIM framework, which highlights essential factors to improving the adoption and implementation of evidence-based interventions: Reach, Efficacy, Adoption, Implementation, and Maintenance [20]. The process evaluation will span the duration of the intervention, as well as pre- and post-intervention evaluation.

## Methods

### Study setting

The intervention will be conducted in the setting of general practices the region of Flanders, Belgium.

### Eligibility criteria

Dutch-speaking GPs working in Flanders and Brussels, Belgium, are eligible to participate. GPs may practice in a group or solo setting, in urban, semi-urban, or rural areas. To reduce contamination risk, one GP per practice will be included. In order to participate, GPs also must be able to identify and include at least 3 eligible patients.

Eligible patients are those with a chronic, life-limiting illness (using indicators described in Table 1) for whom the GP answers “no” to the “surprise question”: “Would I be surprised if this patient were to die within the next 12 to 24 months?” [21]. This one-item screening tool assists in identifying patients with chronic, life-limiting illness who may benefit from the start of an ACP process [22, 23]. Patients for whom the GP would not be surprised if they were to die within the next 6 months will be excluded as the intervention will be tested over a period of 6 months.

**Table 1 Tab1:** Inclusion and exclusion criteria for patients

Patient inclusion criteria	Patient exclusion criteria
Adults (> 18 years old)	Unable to speak or understand Dutch
Mentally competent as measured by judgment of the GP **OR** if Mini-Mental State Examination has been conducted, score is > 24	Unable to provide consent or complete the questionnaires due to cognitive impairment (as judged by the GP)
GP answers “no” to surprise question: “Would I be surprised if this patient were to die within the next 12 to 24 months?”	GP answers “no” to surprise question: “Would I be surprised if this patient were to die within the next 6 months?”
Diagnosis of a life-limiting illness: 1. Locally-advanced unresectable, or metastasized **cancer** OR 2. **Organ failure,** this being a) heart failure (New York Heart Association stage 3 or stage 4) b) chronic kidney failure or end-stage renal disease (ESRD) (stage 4, eGFR = 15–29; or stage 5, eGFR< 15) c) Very severe COPD (GOLD COPD stages stage 3 or stage 4) OR 3. **Geriatric frailty** (Clinical Frailty Scale score 5–7, mildly to severely frail)	Participated in the pilot study of this intervention or in the cognitive testing of the adjusted intervention materials
	Participating in other studies evaluating advance care planning, palliative care services or communication strategies
**SDM inclusion criteria**	**SDM exclusion criteria**
Adults (> 18 years old)	Unable to speak or understand Dutch
Identified by the patient as their surrogate decision maker OR as a person who may be willing to be their surrogate decision maker	Unable to provide informed consent

The patient may identify their SDM for inclusion, or they may designate someone who may be willing to act as their SDM; the latter is the potential SDM. Through the rest of this manuscript, “SDM” will refer to both the SDM and the potential SDM. While patients are encouraged to identify a SDM for participation, not identifying one will not exclude the patient from participation.

All inclusion criteria for patients and their SDM can be found in Table 1.

### Intervention and control

#### Intervention

The ACP-GP intervention (Table 2) is designed to 1) train GPs to conduct ACP discussions with eligible patients, 2) prepare patients for the conversation by providing them with a workbook about ACP, 3) facilitate at least 2 ACP conversations between GP and patient (and SDM if present), and 4) document the outcomes of the discussion in the patient electronic medical file with the help of a structured template.

**Table 2 Tab2:** Key elements of the ACP-GP intervention

1. GP training	The GP training, which has been tested multiple times, is originally conceptualized as two interactive sessions of 3 h each, delivered to small groups of 6–8 GPs at a time within the university hospital setting or another location that is convenient for the participants. However, due to COVID-19 concerns, the content of the training has been translated to an online platform. The training is provided by a trainer experienced in primary care and communication. Two interactive web sessions of approximately 2 h each will replace the live sessions. Preparatory activities such as fictional case examples with reflection questions will be available before the training begins. GPs will have access to background information portions through an e-learning module presented via the Ufora platform of the Universiteit Gent. This module will take no more than 60 min to review. The first aim, improving ACP knowledge, will be addressed via the e-learning module. ACP communication skills will be practiced with video role-modeling exercises which are available on the e-learning module and will be further elaborated on during the web sessions. These web sessions will also include role-play exercises with model patients and interactive discussions with fellow GPs and the trainer. During the training, GPs will receive an extensive conversation guide and an at-a-glance conversation flowchart. These can be used as preparation for and during ACP conversations with patients. In the context of their continuous medical education, GPs will be able to obtain accreditation in ethics and economy by following the training. GPs in the control group will have the opportunity to follow the training after the conclusion of the study, so that both groups have access to this incentive. After the training sessions, GPs will have the opportunity for check-in discussions with the trainers to ask questions and report issues.
2. ACP workbook for patients	During the first home visit, the RA will give patients an ACP workbook that highlights the importance of ACP at different stages of health. The workbook contains questions to stimulate reflection on topics such as quality of life and preferences for future care. The workbook is adjusted for health literacy and has been evaluated through cognitive interviewing with 6 patients who fulfill the inclusion criteria of the trial.
3. Patient-centered ACP discussion with conversation guide	After the training, the GP will conduct a minimum of two ACP conversations in the patient’s home or in the GP office. If COVID-19 safety concerns prohibit the GP from speaking face-to-face with the patient, a telephone consultation or video-consult via an accredited electronic health record software package is also possible. The first conversation takes place within 2 weeks after the GP has received the training; the second within a month after the first conversation. The GP can use the conversation guide, which contains parallel topics to the patient workbook, to structure the conversation. First, the patient is invited to talk about the questions and topics they saw as most important. Then, if time permits, the conversation moves to the questions that have not yet been discussed Patients can choose to have their SDM present at these conversations. If the patient has not yet identified an SDM, they will be encouraged to think about who might be a good fit for this role. Other already-available documents, such as advance directive forms or patient guide materials such as the information booklet provided by the LevensEinde Informatie Forum (LEIF), may be used as the GP or patients see fit. The ACP discussion is expected to last up to 60 min, but GPs are advised during the training to judge the optimal duration according to the openness and engagement of the patient.
4. Documentation of the ACP discussion	The GP will fill out a template reflecting the outcomes of each ACP conversation. The template is based on the structure of the conversation guide. Here, the GP can freely note what was discussed, even if no concrete care decisions were made. During the training, the GP will be instructed to upload this documentation to the patient’s electronic medical file. With the patient’s permission, this information can be shared with other health providers involved in the patient’s care, such as specialist practitioners and home care nurses

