#### Control: care as usual

The intervention will be compared to a control group, which is care as usual. In this group, participating GPs will not receive the training or the conversation guides, and patients will not receive the workbook developed for the intervention. The control group will also not feature the two planned consultations dedicated specifically to discussing ACP as included in the intervention arm. Participating patients will consult with their GP as they usually do. During these consultations, the topic of ACP may still spontaneously be addressed, either by the GP or patient. Other already-available national documents, such as advance directive forms or patient guide materials, may be used as the GP or patients see fit.

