**Efficacy/effectiveness**	• Primary and secondary outcomes of the RCT	• See primary and secondary outcomes above • Reports of any adverse effects			
**Adoption**	• ACP discussion documents uploaded • Patient use of the work booklet • Experiences of GPs and patients applying intervention steps • Changes in GP practice	• Training topic checklist (after each training) • Questionnaire for GPs regarding their ACP practices and conversations in the last 3 months (T1) • Questionnaire for patients regarding ACP conversations with their GP in the last 3 months (T1) • Documentation template review (T1, T2) • Contents of work booklet from a sample of patients in the intervention group (physical copy or digital scan) (T1, T2) • Check-in discussions between GPs and trainers (continuous) • Focus groups with GPs (after T2) • Semi-structured interviews with patients and SDM (after T2)			
**Implementation**	• Fidelity: the extent to which the steps of the intervention were followed as specified in the protocol • Patient and GP barriers/facilitators to following the steps of the intervention • Satisfaction of GPs and patients with the intervention components	• Training topic checklist (after each training) • Check-in discussions between GP and trainers (continuous) • Audio recordings of ACP consultations between GP and patient (and SDM if present) • Documentation template review (T1, T2) • Satisfaction questionnaire for intervention GPs and patients (T1) • Focus groups with GPs (after T2) • Semi-structured interviews with patients and SDM (after T2)			
**Maintenance**	• GP intention for using the intervention materials in the future • Recommendations by the GP and patients to improve intervention usability in the future	• Satisfaction questionnaires for intervention GPs and patients (T1) • Focus groups with GPs (after T2) • Semi-structured interviews with patients and SDM (after T2)			

We have two separate primary outcomes, one at the GP level and one at the patient level. Success on any one of these outcomes at T1 may support a conclusion of effectiveness. Hence there are several ways for the study to successfully demonstrate a treatment effect. This multiplicity problem has been taken into account in the power analysis by controlling the Type I error rate at 2.5% (Bonferroni method).

Scores on the ACP Engagement Survey and the ACP Self-Efficacy Scale for GPs will also be measured at T2. We will treat T2 scores on these scales as a secondary outcome.

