### Assignment of interventions

#### Allocation

Randomization will be performed at the level of the GP to avoid contamination bias. Every GP will have to recruit at least three patients. Once three patients have been recruited, the GP will be randomized to either the intervention or control group according to a 1:1 allocation ratio per a computer-generated randomization list. We will use permuted block randomization with varying block sizes. No stratification factors will be taken into account.

Participants will be enrolled to the study by the research assistants and data managers. The allocation sequence will be generated by independent statisticians working with the Biostatistics Unit at the Faculty of Medicine and Health Sciences of Ghent University. Assignment to intervention or control groups of GP-patient clusters will be performed by a researcher not involved with any other portion of this study.

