#### Blinding

Due to the nature of the intervention, neither GP, patient, nor SDM participants can be blinded to allocation. Although the participants cannot be blinded to their assignment and researchers will be unblinded to GP assignment through the coordination of the training sessions, data collection at T0, T1, and T2 will be performed by an independent data collector/research assistant who is blinded to the assignment of the GP and patient to either the intervention or control arm. Those performing the data analysis will likewise remain blind to participant allocation.

Informed consent and data collection at T0 will occur before randomization has taken place.

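### When, and by whom, the patient workbook is handed over conflicts with randomisation after T0 and with the claim of a blinded data collector

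*Protocol article*

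**What the plan says.** The statements stand in different sections of the protocol article.

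- **Table 2, item 2 (workbook):** "During the first home visit, the RA will give patients an ACP workbook".
- **Control: care as usual:** in this arm "patients will not receive the workbook developed for the intervention".
- **Allocation:** "Once three patients have been recruited, the GP will be randomized to either the intervention or control group". Research assistants and data managers enrol the participants.
- **Blinding:** "Informed consent and data collection at T0 will occur before randomization has taken place". The same section says that "data collection at T0, T1, and T2 will be performed by an independent data collector/research assistant who is blinded to the assignment". The only staff it names as unblinded are the researchers, because they coordinate the training sessions.
- **Recruitment, Patients and SDMs:** the research team informs the patient at home, at another convenient place or by telephone. RAs help the patient name a surrogate at the visit.
- **Participant timeline:** T0 follows consent. At T1 it is the RA who approaches patient and surrogate.
- **Data collection methods:** patients can have help with the T0 and T1 questionnaires from a data manager, in person or by telephone.
- **Table 3, process evaluation:** the measures include "Satisfaction questionnaire for intervention GPs and patients (T1") and the contents of workbooks from a sample of intervention patients at T1 and T2.

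**The concern.** Table 2 fixes both a time (the first home visit) and a person (the RA) for handing over one of the four components of the intervention. Other sections fix when randomisation happens, who may not receive the workbook, and who must stay blinded. These rules do not fit together.

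Two things are at stake. First, the workbook is meant to prompt reflection on future care, and the patient primary outcome is engagement with advance care planning. A control patient who received the workbook would have been exposed to part of the intervention, which would tend to shrink the T1 difference. If it were handed over before the T0 questionnaires, it could also shift the baseline in either arm. Second, the patient primary outcome is self-reported, with staff support available at T1. If the person giving that support had earlier delivered the workbook, the stated blinding of data collection would not hold for those patients. T2 patient questionnaires come back by post, so T1, the primary time point, is where this matters most.

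**Working it through.** No figure in the plan is under test, so the check compares sequence and roles across sections.

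**Step 1: which visit is the first home visit?** The article does not define the term. Before T1 it describes one kind of patient visit: the research team's information visit (Recruitment, Patients), at which RAs help identify a surrogate (Recruitment, SDMs), together with T0 completion, for which in-person help is offered (Data collection methods). No later visit for delivering materials is described in the text. The natural reading is therefore the recruitment and baseline contact. This is an inference, because the paragraph on patient recruitment uses neither the term first home visit nor T0.

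**Step 2: is the arm known at that contact?** No. The GP is randomised only after the third patient is recruited (Allocation), and consent and T0 come before randomisation (Blinding).

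**Step 3: what follows if the workbook is given at that contact?** Handover cannot be restricted to one arm. Either patients of GPs later allocated to control also receive it, against the section on the control arm, or allocation is already known, against the Blinding section.

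**Step 4: what follows if a later visit is meant?** Handover can then be restricted to intervention patients, but whoever delivers the workbook knows the arm. Table 2 names the RA. The Participant timeline gives the T1 contact to the RA, and the Blinding section describes the collector as an "independent data collector/research assistant who is blinded to the assignment of the GP and patient". Nothing in the text separates these roles, and the one acknowledged route of staff unblinding is the coordination of training.

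| Reading of the first home visit | Rule it collides with |
|---|---|
| Recruitment/T0 contact, workbook to all | Control patients do not receive the workbook |
| Recruitment/T0 contact, workbook to one arm | Consent and T0 precede randomisation |
| Later visit, same RA as at T1 | Data collector blinded at T0, T1 and T2 |
| Later visit, separate unblinded RA | None, but no such person or visit is described |

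**Step 5: how many patients?** The Sample size section plans 54 patients per group. At most 54 control patients could be exposed under the first row. Under the third row, the collector would know the arm of at most 54 intervention patients through delivery itself. These are ceilings on the number of patients concerned, not estimates of bias.

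**The case against.** The strongest reply is that the sections, read together, already give the answer. The workbook sentence sits in a table of intervention elements, the control section bars the workbook from controls, and randomisation follows T0. So the workbook must go to intervention patients after allocation. The collector is called independent, several staff roles are mentioned, and a separate unblinded RA could make the delivery. The flow diagram (Fig. 1), not available for this review, may show when delivery takes place, and a condensed article need not give every logistic detail.

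Much of this stands. It shows that exposure of controls is unlikely to be intended and that one consistent arrangement exists. It does not remove the conflict, because the article does not merely leave the detail out. It names a visit and a role, and both collide with rules stated elsewhere. Restricting the workbook to one arm is exactly what requires the person handing it over to know the arm.

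Four stronger readings are tempting and not supported:

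- **The design forces either contamination or unblinding.** The fourth row of the table above is a way out, although it is not described.
- **All 108 patients become unblinded to the collector.** That assumes a single RA who delivers every workbook and collects all T1 data. The article speaks of RAs in the plural.
- **The RA completes the T1 questionnaires with the patient.** Support is assigned to a data manager, and elsewhere to data collectors. The text gives the RA only the T1 approach.
- **The intervention-only satisfaction questionnaire and workbook copies reveal the arm to the collector.** Table 3 does not say who gathers them or in what order, so this is a conditional risk.

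It is also true that patients cannot be blinded and may disclose their arm to a collector. The article admits that participants are unblinded. This limits what collector blinding can achieve, but it does not excuse a procedure that would itself unblind the collector.

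**Conclusion.** The concern holds as a conflict between stated rules: the sections disagree on when the workbook is delivered and by whom. Followed literally, they carry a risk of control exposure or of an unblinded collector at T1. The conclusion rests on two points. The recruitment and baseline contact is the only patient visit before T1 in the text, and the same role term is used for workbook delivery, T1 contact and blinded collection. If the full protocol or the flow diagram describes a separate post-randomisation delivery by other staff, the article only needs to say so.

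The number of patients concerned is at most 54 in either arm. The size of any bias cannot be quantified from the document, and neither the sample size nor the planned analysis is called into question. It still merits correction before patients are visited, because it touches the primary contrast and the blinding claim.

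**What to change.** Reconcile Table 2, item 2 with the sections on the control arm, Participant timeline, Allocation and Blinding. State that:

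1. the workbook goes only to patients in the intervention arm;
2. it is delivered after T0 is complete and after the patient's GP cluster has been randomised;
3. it is sent by post or given by the researcher who is already unblinded through coordinating the training, and not by the person who collects T0 or T1 outcomes.

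Use distinct terms for the person who delivers materials and the person who collects outcomes, and list workbook delivery among the acknowledged routes of staff unblinding.

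As a secondary precaution, have the intervention-only satisfaction questionnaire and the workbook copies handled by someone other than the blinded collector, or only after the outcome scales have been completed.

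The cost is a wording change and a mailing, with no extra staff and no change to sample size or analysis.
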